## Abstract

**Aim:** This study aims to build the capacity of the people at grass root level as gatekeepers of mental health. It will assess the effectiveness of the Gatekeeper Training Program (GTP) on gatekeeper behaviour, awareness, attitude, and mental help seeking intention.

**Design:** An evaluative research approach in two phases. Phase 1: Cross-sectional house-to-house exploratory survey. Phase 2: A quasi-experimental design with multiple follow ups at 0, 6 and 12 months.

**Method:** Data will be collected using standardized tools like Mental Health Knowledge Questionnaire (MHKQ), Community Attitude towards Mentally Ill (CAMIS), Mental Help Seeking Intention (MHSIS) and Gatekeeper Behavior Scale (GBS). For Phase 1, a house-to-house survey will be conducted among the selected colonies of Koraga tribe to determine their awareness, attitude, and mental help seeking intention regarding common mental health problems. Phase 2 includes identification of the leaders/representatives of the selected tribal colonies, and involving them in GTP. Pre-test and multiple post-test will be conducted in Phase 2 at 0, 6, 12 months.  The study is funded by Indian Council of Medical Research from 16 August 2021 for 3 years duration.

**Discussion:** Treatment gap in psychiatric disorders remains an issue of great concern. Evidence based research promotes task shifting approaches in dealing with mental health problems in the community. Capacity building programs like GTP for the underprivileged section of the society are important especially in low and middle income group of countries.

**Impact:** This need based GTP, will ensure mental health first aid in the society. Early identification of people with mental health problems at their doorsteps has huge impact on the prognosis of the illness, closing the treatment gap and stigma reduction.

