The Systematic Medical Appraisal, Referral and Treatment (SMART) mental health project of Andhra Pradesh found that 7% of people go to faith healers and religious leaders at the very beginning of their mental illness for treatment (
Maulik *et al.*, 2017). The preference for magico-religious healing and traditional practices to overcome mental health concerns is prevalent in South-Asian countries, evidenced by a qualitative study from Bangladesh on tribal communities (
Rahman *et al.*, 2012). As mentioned earlier, the study poses a challenge to the healthcare delivery system in low-income countries, which mainly caters to the plainland population. A randomized controlled trial across 32 colleges of USA evaluated the effectiveness of the gatekeepers training program and found that trainees' self-perceived knowledge, ability, and confidence to identify students in distress were increased (
Lipson *et al.*, 2014). In the long-term effects of community gatekeeper training, 15 (n=40) participants had helped someone at risk of suicide; also, intentions to help and confidence to identify someone at risk of suicide remained high (
Deane *et al.*, 2006). Though common mental health problems are prevalent among the tribal population, as evident by the research studies mentioned above, very little is done to improve their condition in India. Hence, it is vital to improve the mental health care system for our most primitive and underprivileged tribal people and develop effective mental health care programs at the grassroots level.

**Aims and Objectives:** The objectives of the study are to:
•Determine the awareness, attitude and mental help seeking intention regarding common mental health problems among the tribal population using standardized tools.•Assess the awareness, attitude, mental-help seeking intention and gatekeeper behavior among the leaders/representatives of Koraga tribe regarding common mental health problems using standardized tools.•Find out the effectiveness of gatekeeper training program on awareness, attitude, mental help seeking intention and gatekeeper behavior among the leaders/representatives of Koraga tribe regarding common mental health problems.•Determine the number of vulnerable individuals identified, counselled, referred to a tertiary center as and when needed by the trained gatekeepers of the tribal community at 12 months of follow up.

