### Setting and population

The study will be conducted in Koraga tribal colonies of Udupi district, Karnataka. There are around 360 colonies spread across seven blocks of the Udupi district, and each colony comprises a minimum of 8-10 families. The colonies are geographically distinct in nature. The total Koraga population is 11,133 in Udupi district. Variables under Phase 1 of the study will be awareness, attitude, and mental help seeking intention and Phase 2 variables include awareness, attitude, mental help seeking intention and gatekeeper behavior regarding common mental health problems.

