### Sample size

Phase 1 sample size is calculated using the formula as mentioned below. In this formula the confidence level is 95%, hence Z
^2^ = 1.96. Here proportion of the tribal people having awareness regarding common mental health problems was assumed to be 0.5 and (d) is the precision of the study (corresponding to the effect size) = 0.05.

$$n=\frac{Z^{2}P\;\left(1-P\right)}{d^{2}}=384\approx 400$$

For Phase 2: Using G* power software the sample size was estimated to be 86 (43 in each group).

With 20% attrition rate n = 108 (54 in each group).

(Here the values are as follows: Effect size = 0.25, Alpha error = 0.05, power = 0.8, Number of groups = 2, Number of measures = 3.)

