### Data collection

For Phase 1 data will be collected using standardised tools like Mental Health Knowledge Questionnaire (MHKQ), Community Attitude towards Mentally Ill scale (CAMIS), and Mental Help Seeking Intention scale (MHSIS). Administrative permissions for the data collection is obtained. The data will be collected from the participants after explaining the participant information sheet and obtaining informed consent. Data collection will be carried over six months due to geographical constraints.

For Phase 2, identification of the participants for the GTP i.e the leaders/representatives of the selected tribal colonies will be done with the help of Department of Tribal Welfare, at the district administrative office. The project staff will approach the selected leaders/representatives of the tribal colonies, explain the participant information sheet, obtain consent and then proceed with data collection. Data for pre-test and multiple post-test (at 0, 6, 12 months) will be collected using standarised tools such as MHKQ, CAMIS, MHSIS and Gatekeeper Behavior Scale (GBS). The project staff will be present during the data collection procedure in both phases of the study.

Confidentiality of the data collected: The consent forms will be coded, and any identification data will be concealed thoroughly for both phase 1 and phase 2. The data collection for phase 1 will be done through house-to-house survey using structured questionnaires and data collection for phase 2 of the study will be done during the GTP, that is, the two-day workshop. Structured questionnaires will be used to collect the data. There is no in-depth interviews or verbatim reports involved in this study, however if the participants need any clarifications while filling out the structured tools, the primary investigator will be there to clarify it.

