**Ethical consideration:** Permission to conduct the study is received from the Head of the Institution, Institution Review Committee and Institutional Ethics Committee (322/2020). Permission is also obtained from the tribal community authority (Integrated Tribal Development Office) at the district government office of Udupi. This study is registered in Clinical Trial Registry of India (CTRI/2021/06/034037 [Registered on: 07/06/2021]. Informed consent will be obtained from all participants, and a complete explanation of the investigation will be provided.

Participation in this study is voluntary; the participants may decline to participate at any time, and they need not give any reason for the same, and such withdrawal shall be without penalty. If they withdraw from the study before data collection is completed, the data collected until they indicated withdrawal will be used in the study report. The sample size is calculated by keeping in mind the attrition rate at 20%, hence the sample size will not be affected with the drop-outs.

**Data analysis:** Demographic characteristics of the study participants will be presented in descriptive summary tables. The outcome variables across the follow up period will be analyzed by repeated measures of ANOVA. The categorical variables will undergo bivariate analysis by applying the Chi-square test for categorical variables. A p-value of less than 0.05 will be considered the criteria for statistical significance. Overall SPSS 26 version will be used to analyse the data gathered.

**Dissemination of results:** The results will be disseminated via presentations at appropriate scientific conferences and workshops. The findings will also be published in peer-reviewed journals, professional and institutional repositories etc. The result will be discussed with the Department of Tribal Welfare and other stakeholders for improvement of mental health awareness, accessibility to meantal health care and appropriate utilization of community-based resources.

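### Phase 2 tests four unranked effectiveness outcomes, each at an unadjusted 0.05, but its sample size covers one test on an unnamed outcome

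*Protocol article*

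**What the plan says.** The third objective in the protocol article is to "Find out the effectiveness of gatekeeper training program on awareness, attitude, mental help seeking intention and gatekeeper behavior". The Abstract gives the aim as the "effectiveness of the Gatekeeper Training Program (GTP) on gatekeeper behaviour, awareness, attitude, and mental help seeking intention", so gatekeeper behaviour comes first there and last in the objectives. Setting and population states that "Phase 2 variables include awareness, attitude, mental help seeking intention and gatekeeper behavior". Data collection assigns one scale to each: MHKQ, CAMIS, MHSIS and GBS. No outcome is called primary.

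Data analysis states: "The outcome variables across the follow up period will be analyzed by repeated measures of ANOVA". Apart from chi-square tests for categorical variables, the only further rule is "A p-value of less than 0.05 will be considered the criteria for statistical significance".

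Sample size gives one set of inputs for Phase 2: "Effect size = 0.25, Alpha error = 0.05, power = 0.8", with two groups and three measures. The result is 86 participants (43 per group), or 108 (54 per group) with 20% attrition. No outcome is attached to the effect size.

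**The concern.** These three parts do not fit together. The objective and the analysis set up four parallel tests at 0.05. The sample size is calculated as if there were one. The reader cannot tell which scale the 80% power protects, or what pattern of results would count as the programme working.

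This matters because the results are to be discussed with the Department of Tribal Welfare and other stakeholders. With four unranked outcomes, a report could lead with whichever scale reached significance, and nothing in the article would show that this scale was chosen after the results were known.

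**Working it through.** **Inputs.** From Sample size: effect size 0.25 (read as Cohen's f), alpha 0.05, power 0.80, 2 groups, m = 3 measures, attrition 20%. From the objectives: 4 outcomes. From Data analysis: p < 0.05, no adjustment stated. Two inputs are not in the article and are assumed: the correlation ρ between repeated measures (0.5, the software default) and the correlation r between the four outcomes (shown over a range).

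**1. Reproduce the stated sample size.** For the between-group F test in a repeated-measures ANOVA, with 1 and N − 2 degrees of freedom:

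λ = f² × N × m / (1 + (m − 1)ρ)

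- N = 86: λ = 0.0625 × 86 × 3 / 2 = 8.06, power 80.1%.
- N = 84: power 79.2%, so 86 is the smallest even N reaching 80%.
- Attrition: 86 / 0.8 = 107.5, rounded up to 108.

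Both stated figures reproduce. A within-subject or group-by-time test with the same inputs would need only 28. The 86 is therefore the size for one between-group F test at the full alpha. With ρ = 0.3 or 0.7, that test would need 70 or 104.

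**2. False positives if any one of four is enough.** With independent outcomes and no true effect:

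1 − (1 − 0.05)⁴ = 1 − 0.8145 = 18.5%

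For four equally correlated normal test statistics, by numerical integration:

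| Correlation r between outcomes | At least one p < 0.05, either direction | At least one p < 0.05, favourable direction only |
|---|---|---|
| 0 | 18.5% | 9.6% |
| 0.3 | 17.4% | 8.7% |
| 0.5 | 15.6% | 7.8% |
| 0.7 | 13.0% | 6.5% |
| 0.9 | 9.4% | 4.7% |
| Single test | 5% | 2.5% |

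This counts one F test per outcome.

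**3. Power if all four are required.** The false-positive rate is then at most 5%. If each scale had a true effect of f = 0.25 and 80% power, joint power would be 0.8⁴ = 41% for independent outcomes. It would rise towards 80% only as the outcomes became perfectly correlated.

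**4. Splitting alpha over four co-primary outcomes.** At 0.05 / 4 = 0.0125 each, the independent error rate is 1 − 0.9875⁴ = 4.9%. The formula in step 1 then gives 61% power per outcome with 86 completers. Reaching 80% needs 124 completers, or 124 / 0.8 = 155 with attrition.

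**5. A single time point as primary.** With m = 1, λ = 0.0625 × 86 = 5.375 and power is 63%. Reaching 80% needs 128 completers, or 128 / 0.8 = 160 with attrition.

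**The case against.** The strongest reply is that a significance criterion is not a decision rule. The article nowhere says that one significant scale shows the programme to be effective. The objective can be read as four separate questions, each answered with 5% error, or as a claim that needs all four. This stands: the rates in step 2 depend on an assumed success rule and should be quoted as conditional. It does not remove the problem, because on no reading is it clear which outcome the 80% power refers to, and on the all-four reading that figure is not the power of the claim.

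A reader might infer that a false claim of benefit has a 16–19% chance. The documents do not support that as a flat statement. It needs the any-one rule and outcome correlations no higher than about 0.5, and it counts significance in either direction. Counting favourable results only, the range over the same correlations is 7.8% to 9.6%, against 2.5% for one test.

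A reader might also infer extra tests at each post-test or on the CAMIS and GBS subscales. Data analysis plans neither: it describes a joint analysis over follow-up, and the subscales appear only in the description of the instruments.

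Finally, adjustment methods are often left to an analysis plan, and none is shown here. That is fair for the detail of the method. The point rests instead on what the article does fix: four unranked outcomes, one unadjusted threshold, and a one-test sample size with no outcome named.

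**Conclusion.** The concern holds in a limited form. The sample-size arithmetic is sound for one between-group test at an assumed ρ of 0.5, but the plan lists four such outcomes and does not say which one that test concerns. Under an any-one-is-enough rule, the two-sided chance of at least one false positive is 18.5% at r = 0, 15.6% at r = 0.5 and 9.4% at r = 0.9. That is above 5% throughout this range, though the exact figure is unknown because the article gives neither the rule nor the correlations. Under an all-four rule there is no inflation, but the stated power does not carry over. Study status says data collection has not begun, so a primary outcome can still be chosen without knowledge of results.

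**What to change.** Before data collection, add a short paragraph to Data analysis and one sentence to Sample size:

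- Name one primary outcome. The GBS total is a reasonable example because gatekeeping is what the programme trains; the sponsor may choose another.
- Test it at 0.05 by the between-group effect of the repeated-measures ANOVA over three measures, and say which three measures these are.
- State that the 86 completers (108 with attrition) refer to this test, and give the assumed effect size (f = 0.25) and between-measure correlation (0.5).
- Treat the other three scales as secondary with Holm adjustment, and claim them as confirmed only if the primary is significant. Without that condition, the two families could together reach 0.05 + 0.05 = 10%.

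The recruitment target does not change. The cost is a stricter threshold for the secondary scales. The smallest of the three p-values must beat 0.05 / 3 = 0.0167, where the step 1 formula gives about 65% power per scale at f = 0.25 with 86 completers.

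Do not make a single 12-month comparison primary at the present size. At f = 0.25 it would have about 63% power, and restoring 80% would take 160 participants instead of 108.

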## Discussion

The health status of the tribal population is in a pitiable condition (“Tribal Health,” n.d.). They continue to suffer due to inequity and inaccessibility in the health care system (
MOHFW&MOTA, 2013). Traditional healers and magico-religious practices are still popular among the tribal population worldwide (Beals
*et al.*, 2005). The stigma associated with mental illness is another cause for the treatment gap in psychiatry. Innovative and decentralized community-based approaches should be adopted to reduce barriers in vulnerable populations. World Health Organization has recognized informal community care by peers or community people as an effective and low-cost method of providing mental health services to the vulnerable population (
The Optimal Mix of Services, 2007). Atmiyata, a community-based intervention carried out in Gujarat, India, which provides support to people experiencing mental health issues, found significant improvement in recovery rates and overall quality of life (
ATMIYATA: A Community-Led Intervention in Rural India|Mental Health Innovation Network, n.d.).
Nimgaonkar and Menon (2015) in their community-based task-shifting program found that the self-referrals rates increased from 27% to 57%. Also, there was positive growth in knowledge, attitude, and practice about mental health. Hence much more research is required in these areas, and best practices in the community needs to be identified. Community-based interventions incorporating the needs, active participation, socio-cultural beliefs, and resources of its people are reportedly successful.

### Limitations

The desire to commit oneself to social service and help out a person with mental health issues (gatekeeper) vary from person to person and are very subjective in nature. Also in this study the gatekeeper behaviour in the community will be greatly affected by the acceptance of the services despite the stigma, the gatekeepers' belief system, and inter-sectorial coordination among the community stakeholders. Interaction between the gatekeeper and an individual with mental health problems in the community will be collected as a self-report as the researchers cannot reach at the point of time in the community.

## Conclusion

The information obtained on awareness, attitude, and mental-help-seeking intention regarding common mental health problems will help to build the efficacy of Koraga tribe members in terms of gatekeeping behavior. This study believes that community-based interventions are an integral part of mental health services. Programs that help to build the capacity of the people at the grassroot levels will help in early identification, and referral of individuals with signs and symptoms of possible mental health problems, thus reducing the treatment gap, stigma and making mental health services more accessible.

**Study status:**

The researcher is yet to start with the data collection for the study. At present, the tools were validated for cross cultural validity, and pilot phase of the survey is being planned.

## Data availability

### Underlying data

No underlying data is associated with this article.

### Extended data

Extended data available at Figshare repository: The following datasets are available with their doi:
1.Informed Consent for Phase 1.
https://doi.org/10.6084/m9.figshare.19114415.v2 (
[name] *et al.*, 2022a).2.Informed Consent for Phase 2.
https://doi.org/10.6084/m9.figshare.19114409.v1 (
[name] *et al.*, 2022b).3.Participant information sheet for Phase 1.
https://doi.org/10.6084/m9.figshare.19114430.v1 (
[name] *et al.*, 2022c).4.Participant Informant Sheet - Phase II (Experimental group).
https://doi.org/10.6084/m9.figshare.19114412.v1 (
[name] *et al.*, 2022d).5.Participant Information Sheet - Phase 2 for Control group.
https://doi.org/10.6084/m9.figshare.19114421.v1 (
[name] *et al.*, 2022e).6.Background information.
https://doi.org/10.6084/m9.figshare.19114418.v1 (
[name] *et al.*, 2022f).

Data are available under the terms of the
Creative Commons Zero “No rights reserved” data waiver (CC0 1.0 Public domain dedication).
